### Setting

The ABCR treatment and control treatment will take place at the outpatient clinic, CADIC, Psychiatric Centre Copenhagen, Rigshospitalet. Outcome assessments are performed at CADIC, Psychiatric Centre Copenhagen, Department O, Rigshospitalet.

#### Action-based cognitive remediation

ABCR is a manual CR program developed by [name], Psychology Department, Queen’s University, Kingston, Ontario, Canada. It is traditionally carried out on groups of 4–6 participants with two therapists. The program covers the following cognitive domains: meta-cognition, verbal and visual working memory, memory, attention, and executive functions (organization, shifting attention, and planning). The program is carried out twice a week with each session lasting 2 hours. The program duration is 10 weeks, accompanied by daily computer training at home and homework assignments consisting of cognitively challenging everyday tasks (e.g. organizing stacks of documents, reading the newspaper, and making a budget). The computer program, the Danish version of HappyNeuron Pro (http://www.happyneuronpro.com), is administered on tablets and includes 28 tasks targeting processing speed, selective attention, working memory, verbal and visual learning, reasoning, and problem-solving. The program has 30 difficulty levels, and participants require an 80% success rate to advance to a more challenging level. Prior to the first ABCR session, participants receive an individual goal setting session, including identification of cognitive strengths and weaknesses based on the screening carried out during the eligibility assessment.

The ABCR program begins with an orientation session about the purpose and structure of the treatment and provides an opportunity for participants to state their personal goals to the group. Each session consists of a short presentation of the theme of the day followed by related computer activities and a joint discussion of strategies. Practical everyday-like activities (e.g. planning a meal and scheduling appointments) are then role-played keeping in mind the theme of the day and recently discussed strategies. The everyday-like activities are a main part of the sessions, and are performed using props such as food items, planners, city and amusement park maps etc. to increase the ecological validity of the activities. Each session ends with a discussion of how the content is related to each participant’s individual goal, and by identifying cognitively challenging everyday tasks for the participants to carry out between sessions. For four sessions within the program, the usual structure is replaced by computer training interleaved by 20-min individual goal setting sessions. Treatment completion is defined as 80% attendance and individual catch-up sessions are offered for missed sessions, if logistically possible. Attendance and time spent on the computer exercises between sessions will be recorded.

#### Control treatment

The control treatment is a weekly 1-h conversation group for 10 weeks. The sessions are conducted to control for the therapeutic effects of group treatment and are designed to *avoid* any training of cognitive abilities, but to remain meaningful for participants. Patients discuss their experiences of suffering from BD. There is no set structure in the groups, as relevant themes are suggested by the group leaders but ultimately decided by the participants. Group leaders primarily have a mediating function and serve to reinforce the time limit. A previous study showed that fewer participants dropped out of a group with a similar structure than in a psychoeducation group, which indicates general satisfaction with this group format [30].

### Treatment retention

All participants will receive feedback on the results of their neuropsychological results once they have completed the 6-month follow-up assessment. Additionally, participants randomized to the control group will be offered access to HappyNeuron Pro (www.happyneuronpro.com) following the 6-month follow-up-assessment. Participants who are working will be offered compensation of 100 Danish crowns an hour for 10 h of fMRI and neuropsychological assessments. Travel expenses for public transportation will be reimbursed for all participants.

### Randomization and blinding

Pharma Consulting Group carried out block randomization for each group stratified by gender and age (< or ≥ 35 years). Participants are randomized using a 1:1 allocation ratio. The study is outcome-assessor blind, and the randomization list and allocation envelopes are sealed in opaque envelopes and will be kept in a locked filing cabinet to prevent unblinding. The randomization list will not be opened during the trial enrolment phase or while the data analyses have not been completed. Allocation is carried out by the therapist, who will open the envelopes consecutively within each stratum following each eligibility assessment. Participants will be instructed not to disclose any information concerning their treatment allocation during assessments. Under no circumstances will the allocation be revealed to the outcome assessors.

### Outcome assessments

For an overview of outcome assessment frequency and timing (see Fig. 2). The primary outcome is a broad cognitive composite score, which has been recommended as a primary outcome in cognition trials by the targeting cognition task force of the International Society for Bipolar Disorders (ISBD) [9]. This composite measure comprises the following tests assessing verbal memory, attention, and executive functions: Rey Auditory Verbal Learning Test (RAVLT) [31], Repeatable Battery for the Assessment of Neuropsychological Status (RBANS) Coding [32], verbal fluency with the letter “D” [33], WAIS-III Letter–Number Sequencing [34], Trail Making Test B (TMT B) [35], and Rapid Visual Information Processing (RVP) from the Cambridge Neuropsychological Test Automated Battery (CANTAB) (Cambridge Cognition). The tests in the composite score differ from the exercises included in HappyNeuron Pro. The composite score is derived by averaging the six *z*-transformed test scores.

**Fig. 2 Fig2:**
[figure not shown]
Schedule of enrolment, interventions, and assessments. OTS One Touch Stockings of Cambridge, FAST Functional Assessment Short Test, SWM spatial working memory, RVP Rapid Visual Information Processing, RAVLT Rey Auditory Verbal Learning Test, RBANS Repeatable Battery for the Assessment of Neuropsychological Status, WAIS-III LNS Wechsler Adult Intelligence Scale Version III Letter–Number Sequencing, TMT-A Trail Making Test A, TMT-B Trail Making Test B, UPSA-B Brief Performance-Based Skills Assessment of the University of California, San Diego, SDS Sheehan Disability Scale, AQoL Assessment of Quality of Life, WHOQOL-BREF World Health Organization's Quality of Life Assessment, COBRA Cognitive Complaints in Bipolar Disorder Rating Assessment, WSAS Work and Social Adjustment Scale, WHODAS World Health Organization Disability Assessment Schedule, DART Danish Adult Reading Test, CTQ Child Trauma Questionnaire, SCIP-D Screen for Cognitive Impairment in Psychiatry—Danish version

Secondary cognitive outcome measures are the One Touch Stockings of Cambridge (Cambridge Cognition, CANTAB), which assesses executive functions, and for assessment of functional capacity, the Functional Assessment Short Test (FAST) [36].

The tertiary (explorative) cognitive outcome measures are the RAVLT, RBANS Coding, verbal fluency with the letters “D” and “S”, WAIS-III Letter-Number Sequencing, RBANS Digit Span [32], TMT B and TMT A [35], RVP, and the Spatial Working Memory (Cambridge Cognition, CANTAB) (cognition). Tertiary (explorative) outcomes of objective functional capacity, quality of life, and subjective functioning in daily life are the Brief Performance-Based Skills Assessment of the University of California, San Diego (UPSA-B) [37, 38], the Sheehan Disability Scale (SDS) [39], the Assessment of Quality of Life [40], the World Health Organization's Quality of Life Assessment (WHOQOL-BREF) [41], Cognitive Complaints in Bipolar Disorder Rating Assessment (COBRA) [42], and the Work and Social Adjustment Scale (WSAS) [43].

The cognition outcomes are in line with the latest recommendations from the Targeting Cognition Task Force of the ISBD [44]. Specifically, the recommendations are to include a cognitive composite score as the primary outcome, a single intervention-specific cognition measure as a secondary outcome, and the multiple individual cognition measures as tertiary (exploratory) outcomes. The functional outcomes also agree with the Targeting Cognition Task Force of the ISBD, which recommends FAST or UPSA-B as secondary outcomes. FAST was specified as the secondary functional outcome in this trial since we have previously demonstrated an association between objective cognition and functional capacity measures using it [17]. SDS and WSAS were selected to examine patient-reported outcomes of disability and work function.

#### Peripheral and neural biomarkers and genotype

To assess hypothesis (ii), that early changes in neural activity in the dlPFC may predict pro-cognitive effects of ABCR, participants will undergo fMRI scans at baseline and following 4 weeks of treatment (four active ABCR sessions twice a week or control group sessions twice a week). Blood tests are taken at baseline to investigate any neurobiological predictors of potential pro-cognitive effects of ABCR, including high-sensitivity C-reactive protein (hsCRP), inflammatory and metabolic parameters (lipid status and blood glucose level) [45–49]. These samples will also be used to assess potential differences between genotypes of relevance for cognition, such as the Catechol-O-methyltransferase (*COMT*: val158Met) and Brain-Derived Neurotrophic Factor (*BDNF*: val66Met), relating to treatment-associated improvements in cognition.

### Statistical analyses

Data from the neuropsychological, subjective cognitive impairment, quality of life, level of functioning, and psychosocial function assessments will be analyzed using mixed models. Intention-to-treat analyses will be performed for missing data. The data will be analyzed for every participant for all assessments. No interim analyses will be carried out due to the nature and size of the study.

#### Functional MRI analyses

fMRI data will be preprocessed and analyzed with the FMRIB Expert Analysis Tool (FEAT) and the “randomize” algorithm implemented in the FMRIB Software Library. Neuropsychological and fMRI data from cognitively intact healthy controls without prior or current mental illness or mental illness amongst first-degree relatives from the Bipolar Illness Onset study will be used for baseline comparisons.

#### N-back working memory tasks

fMRI data from the N-back working memory tasks will be analyzed using a region-of-interest analysis to assess differences between the ABCR and control groups in neural activity in the dlPFC after 2 weeks (adjusting for any differences in neural differences at baseline). In addition, we will conduct volume-of-interest analyses of the dorsal prefrontal cortex to examine our hypothesis. Exploratory whole-brain analyses will be conducted to investigate any effects in other brain regions.

#### Strategic picture encoding

We will conduct volume-of-interest analyses of the dorsal prefrontal cortex and the hippocampi to assess the fMRI data from the strategic picture encoding task. Finally, exploratory whole-brain analyses will be conducted to investigate any effects in other brain regions.

Any differences in neural activity will be correlated with potential changes in the cognitive composite score after 2 weeks of treatment and post-treatment. If there is a significant correlation with cognition at post-treatment, multiple regression analysis will be carried out, adjusting for mood and demographic characteristics, to assess whether early changes in neural activity are predictive of pro-cognitive effects.

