### Aims and hypotheses

This study aims to assess the effect of ABCR vs. a control treatment on cognitive improvement in (i) BD patients in full or partial remission and to (ii) assess early neural changes indicative of potential treatment benefits on cognition.

We hypothesize (i) that ABCR vs. a control treatment has a beneficial effect on cognition in patients with BD in full or partial remission (the primary hypothesis of the study). We hypothesize (ii) that this treatment-associated improvement of cognition translates into better functional capacity at the 6-months follow-up assessment (secondary outcome). For the *exploratory* analysis of the neuronal underpinnings of these treatment effects, we hypothesize that ABCR will produce an early change in neural activity in the dorsal prefrontal cortex during working memory and strategic memory encoding in the direction of the prefrontal activity levels seen in a healthy control group (i.e., partial normalization) and this activity will correlate with ABCR-associated improvements in cognitive function.

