### Sample size and power calculation

The power calculation was carried out by Pharma Consulting Group (Uppsala, Sweden) (http://www.pharmaconsultinggroup.com) using SAS, based on findings from a previous randomized controlled trial run by our group assessing the effect of 8 weeks of EPO treatment on the same cognitive composite score [50]. The difference between the EPO and saline-treated groups regarding changes on the cognitive composite score was 0.5 standard deviations (SD) from baseline. In this trial, a clinically relevant difference between the ABCR and the control groups following 10 weeks of treatment is assumed to be 0.4 SD (corresponding to a medium effect size) on the primary outcome, with a mean change in the cognitive composite score of 0.5 SD. The power calculation assumes normally distributed data and uses two-sided sample *t-*tests. With these assumptions, we will achieve a power of >80% to detect a clinically relevant difference between the treatment groups at an alpha level of 0.05 with 26 participants in both the ABCR and control groups, respectively. Assuming a 10% drop-out rate from baseline to treatment completion, we will recruit up to 58 participants to achieve complete data sets for 52 participants.

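### The neural-predictor regression names mood and demographics but not treatment arm, so if the arms are pooled, an ABCR effect on both measures can pass for prediction

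*Protocol article*

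**What the plan says.** Under N-back working memory tasks, the protocol article defines the neural result as the ABCR-versus-control difference in dorsolateral prefrontal activity at 2 weeks. The closing paragraph of Strategic picture encoding, which appears to cover both tasks, gives the link to cognition: "Any differences in neural activity will be correlated with potential changes in the cognitive composite score after 2 weeks of treatment and post-treatment". The next sentence sets the second step and its covariates: "If there is a significant correlation with cognition at post-treatment, multiple regression analysis will be carried out, adjusting for mood and demographic characteristics". The stated purpose of that step is to judge whether early neural change predicts pro-cognitive effects.

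The functional MRI sections do not name treatment arm as a covariate, specify an analysis within arm, or say whether the arms are pooled. Aims and hypotheses labels this work exploratory. It expects ABCR to improve cognition and to shift dorsal prefrontal activity early, and adds that "this activity will correlate with ABCR-associated improvements in cognitive function".

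**The concern.** The trial's own hypotheses make treatment arm a common cause of both variables. If ABCR moves prefrontal activity and also moves the composite, ABCR patients sit higher on both and controls lower on both. Pooled over the sample, the two measures then correlate even if, within each arm, a patient's neural change says nothing about that patient's cognitive change. Adjusting for mood and demographics does not remove this, because randomization makes baseline characteristics unrelated to arm on average.

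The interpretation of the week-2 scan is at stake. Procedure says the scan is repeated to see whether early neural change correlates with and predicts later improvement, and the Discussion looks towards a biomarker model. Under the written rule, a treatment that affects both measures separately cannot be told apart from early neural change that carries information about cognitive gain. The confusion grows with the size of the ABCR effects.

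**Working it through.** **Inputs**
- Sample, alpha and power, from Sample size and power calculation: "at an alpha level of 0.05 with 26 participants in both the ABCR and control groups", and "we will achieve a power of >80% to detect a clinically relevant difference between the treatment groups".
- Cognitive effect, same section: the difference "is assumed to be 0.4 SD (corresponding to a medium effect size) on the primary outcome". A second figure, 0.5, is described there as a mean change.
- Neural effect: the article gives none. Assumed here as 0.5 to 1.2 within-arm SD.
- Within-arm association between neural change and cognitive change: set to zero, so that every declared predictor is false.

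**Step 1: reproduce the plan's figure.** With a difference of 0.4 and an SD of change of 0.5, the standardized effect is 0.4/0.5 = 0.8. At 26 per arm the noncentrality is 0.8 × √(26/2) = 2.88 on 50 degrees of freedom, and the exact two-sided power is 80.7% (82.2% by normal approximation). Dropout: 52/(1 − 0.10) = 57.8, so 58. The stated figures reproduce when 0.5 is read as the SD of change. If 0.4 is itself the standardized effect, power is about 29%. The plan's own cognitive effect is therefore taken as 0.8 within-arm SD, with 0.4 as a lower case.

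**Step 2: correlation produced by arm alone.** Let dN and dC be the arm effects on neural change and cognitive change in within-arm SDs. With 1:1 allocation the arm indicator has variance 1/4. The pooled covariance is then dN·dC/4 and each pooled variance is 1 + d²/4, so

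r = (dN·dC/4) / √[(1 + dN²/4)(1 + dC²/4)].

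For dN = dC = 0.8: 0.16/1.16 = 0.14. For dN = 1.2 and dC = 0.8: 0.24/√(1.36 × 1.16) = 0.19.

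**Step 3: false-positive rate of the written rule.** There were 20,000 simulated trials per scenario, 26 per arm, with one mood and one demographic covariate unrelated to arm or to either measure. The two-step rule requires a significant pooled correlation and then a significant neural coefficient adjusted for mood and demographics, each at 0.05. The last column is the same regression with arm added, fitted in every trial.

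| Neural effect (SD) | Cognitive effect (SD) | Pooled r | Raw correlation significant | Two-step rule | Regression with arm |
|---|---|---|---|---|---|
| 0 | 0 | 0 | 5.1% | 4.3% | 5.1% |
| 0 | 0.8 | 0 | 5.1% | 4.1% | 5.0% |
| 0.5 | 0.8 | 0.09 | 9.7% | 8.4% | 4.9% |
| 0.8 | 0.8 | 0.14 | 16.5% | 14.5% | 5.1% |
| 1.0 | 0.8 | 0.17 | 22.7% | 20.1% | 5.2% |
| 1.2 | 0.8 | 0.19 | 27.9% | 25.0% | 4.9% |
| 0.8 | 0.4 | 0.07 | 8.2% | 6.9% | 5.0% |

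If the correlation is examined only after a significant arm difference in neural activity, the two-step rates for neural effects of 0.5, 0.8, 1.0 and 1.2 SD (cognitive effect 0.8 SD) are 12.6%, 16.6%, 20.9% and 25.2%.

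**The case against.** **Pooling is inferred.** The article never says that both arms enter the correlation. The hypothesis refers to improvements associated with ABCR, and the biomarker section refers to effects of ABCR, which could mean the ABCR arm only. There arm is constant and the mechanism vanishes. This stands as a limit. Pooling is still the natural reading, because the neural result is defined as a difference between arms. An ABCR-only correlation would also leave treatment-specific prediction mixed with general prognosis.

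**The article is condensed.** A fuller plan may include arm. But the article states the trigger, the covariates and the inference to be drawn, and that stated set lacks arm.

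**The size is uncertain and the analysis exploratory.** Both are true. The inflation is small when either arm effect is small.

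A reader might also infer more than the text supports:
- *That more than a third of null trials would yield a marker.* A neural effect of 1.5 SD makes the raw pooled correlation significant in about 37% of trials. That is an extreme assumption and counts only the first step.
- *That baseline neural adjustment depends on observed imbalance.* The phrase "adjusting for any differences in neural differences at baseline" is ordinary wording for baseline adjustment and belongs to the N-back group comparison.
- *That voxels are chosen for showing an arm difference.* The regions are pre-defined, and nothing says the correlation uses selected voxels.
- *That the significance condition is itself the source of error.* With arm in the model, keeping that condition lowers the rate to about 3% when there is a cognitive effect.
- *That an arm-by-neural interaction is indispensable.* The aim speaks of changes indicative of benefit. No passage claims a treatment-effect modifier.

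**Conclusion.** The point holds for a pooled analysis. As written, the rule can report early neural change as a predictor when arm alone explains the association. The false-positive rate is about 8% to 25% for a cognitive effect of 0.8 within-arm SD and a neural effect of 0.5 to 1.2 SD, and about 7% for 0.4 and 0.8 SD respectively, against about 5% with arm in the model. These figures rest on three assumptions: that the arms are pooled, that 0.5 is the SD of change, and a neural effect range that the article does not supply. A reader might infer that the trial's main conclusion is at risk. It is not: the primary comparison and its power do not depend on this analysis. The wording should be corrected because the neural question is the trial's second aim and the stated adjustment set leaves out the one variable that the hypotheses link to both measures.

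**What to change.** State whether the correlation uses both arms. If it does, regress the post-treatment composite on baseline composite, treatment arm and baseline-to-week-2 neural change in the pre-defined regions, plus the planned mood and demographic covariates. Fit this model whether or not the raw correlation is significant. Report the within-arm association (the neural slope with arm in the model) with its confidence interval. An arm-by-neural-change term may be reported as well, labelled exploratory.

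The cost is a change of wording and two further model terms, arm and baseline composite. No new data are needed. The interaction, if reported, will have low precision with about 52 patients.

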### Procedure

Upon their first visit to the Copenhagen Affective Disorder Research Center (CADIC), participants are informed about the project and provide written informed consent after which they undergo an eligibility assessment. The written informed consent will be obtained by the first author. Upon inclusion, participants are randomized with stratification for gender and age (< or ≥ 35 years) to either 10 weeks of ABCR (active treatment) or patient group (control treatment). When 4–6 participants have been randomized to a group, baseline assessments will be carried out in the week prior to the first group session. Deterioration in terms of clinical symptoms at the baseline assessment is recorded, but participants are not excluded if their symptoms worsen. The baseline assessment is completed over two days, 1–3 days apart for practical reasons and to avoid attrition.

On day 1, participants’ mood is rated with the Hamilton Depression Rating Scale and Young Mania Rating Scale, followed by a functional magnetic resonance imaging (fMRI) scan encompassing spatial and verbal working memory N-back tasks, a picture encoding task, a resting state, and a structural scan. On day 2, participants attend the research center in the morning for a fasting blood test. A comprehensive neuropsychological test battery is administered by a treatment-blinded outcome assessor. Participants fill in questionnaires concerning subjective cognitive complaints, psychosocial functioning, and quality of life. Functional capacity is assessed using a clinician-rated interview and a performance-based assessment. Finally, sleep quantity and quality in the past 3 days is assessed.

After 2 weeks of ABCR or control treatment, the fMRI, neuropsychological testing, and an assessment of mood and subjective cognition are repeated to assess whether early task-relevant neural activity changes—prior to improvement on the behavioral measures of cognition—correlate with and predict subsequent cognitive improvement after treatment completion. The neuropsychological assessments and questionnaires, as well as assessments of functional capacity and quality of life, are repeated within 2 weeks after treatment completion (primary outcome assessment time), and 6 months after treatment completion. An intermediate clinical mood rating is performed during week 6.

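### The adjusted regression that tests the neural predictor is fitted only after a significant unadjusted correlation, so its reported estimates are selected for size and an association masked by mood can be missed

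*Protocol article*

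**What the plan says.** The rule stands in the protocol article, in the closing paragraph under Strategic picture encoding. First comes a correlation step: "Any differences in neural activity will be correlated with potential changes in the cognitive composite score after 2 weeks of treatment and post-treatment". No adjustment is named there. The adjusted model then depends on the result: "If there is a significant correlation with cognition at post-treatment, multiple regression analysis will be carried out, adjusting for mood and demographic characteristics". Its stated purpose is "to assess whether early changes in neural activity are predictive of pro-cognitive effects". No unconditional version of this regression is described.

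Three other places bear on the reading:
- N-back working memory tasks uses the word for a comparison between arms: "assess differences between the ABCR and control groups in neural activity in the dlPFC after 2 weeks".
- Procedure gives the reason for the week-2 scan as finding out whether early changes in neural activity "correlate with and predict subsequent cognitive improvement after treatment completion".
- Aims and hypotheses labels the neural work exploratory and expects that "this activity will correlate with ABCR-associated improvements in cognitive function".

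**The concern.** The screen uses the unadjusted correlation, although the plan considers mood and demographics important enough to adjust for. Two consequences follow.

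1. A coefficient that is reported only when the raw correlation on the same data is large has been selected for size. It overstates the association on average.
2. If mood works against the association, the raw correlation can be small while the adjusted one is not. The adjusted model is then never fitted.

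The wording of the correlation step adds an uncertainty. If the neural differences are differences between arms, only measures on which the arms differ go forward. A predictor of individual improvement need not differ in mean between arms.

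At stake is the trial's second, exploratory aim. The Discussion ties it to a biomarker model for effects on cognition, and the Abstract to later treatment development. A later trial planned on an inflated association would be too small.

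**Working it through.** **Inputs from the protocol article.** Complete data are planned for 52 participants, 26 per arm (Sample size and power calculation). The stated alpha is 0.05 with two-sided tests, given for the primary comparison. The article gives no figure for the neural predictor analysis, so there is none to reproduce. The sample size itself does reproduce: 52 / 0.9 = 57.8, hence 58 recruited, and a two-sided t-test with 26 per arm, difference 0.4 and 0.5 taken as the SD of change has 80.7% power.

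**Assumptions.** Alpha of 0.05, two-sided, also applies to the correlation. Mood and three further covariates are adjusted for. True associations and mood correlations are not in the documents and are varied.

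**Threshold.** The smallest significant correlation is r = t / √(t² + n − 2).
- n = 52: t = 2.009, so r = 2.009 / √(4.034 + 50) = 0.273.
- n = 26 (one arm only): t = 2.064, so r = 2.064 / √(4.260 + 24) = 0.388.

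**Size of the selection effect.** Simulation with 20,000 runs per row, n = 52, no mood effect. Columns 3 to 5 are mean adjusted (partial) correlations:

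| True value | Screen passed | Always fitted | Fitted after the screen | No screen, significant results only |
|---|---|---|---|---|
| 0.20 | 30% | 0.20 | 0.35 | 0.36 |
| 0.30 | 58% | 0.30 | 0.38 | 0.39 |
| 0.40 | 85% | 0.40 | 0.43 | 0.44 |

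The inflation is 0.35 / 0.20 = 1.75-fold for a true value of 0.20 and 0.43 / 0.40 = 1.08-fold for 0.40. If only one arm were used (n = 26, standardized slopes, mood and two covariates), a true 0.20 is reported on average as 0.47 and a true 0.40 as 0.53.

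**Masking by mood.** Let a be the correlation of mood with neural change, b that of mood with cognitive change, and p the true partial correlation. The raw correlation is r = ab + p√((1 − a²)(1 − b²)). With p = 0.40 and n = 52:

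| a, b | Raw r | Screen passed | Adjusted test significant if always fitted | Significant adjusted result lost |
|---|---|---|---|---|
| 0.4, −0.4 | −0.16 + 0.40 × 0.84 = 0.176 | 24% | 82% | 58% |
| 0.3, −0.3 | −0.09 + 0.40 × 0.91 = 0.274 | 51% | 82% | 31% |
| 0.1, −0.1 | −0.01 + 0.40 × 0.99 = 0.386 | 82% | 82% | 3% |
| −0.3, −0.3 | 0.09 + 0.40 × 0.91 = 0.454 | 93% | 82% | 0.3% |

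Hand check of the first row by Fisher's z: (0.280 − 0.178) × √49 = 0.72, an upper tail of about 24%. With no mood effect at all, the loss is about 1 to 3%.

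**False positives.** With no true association, the screen passes in about 5% of runs, and about 75% of those are also significant after adjustment. Both steps are passed in 0.05 × 0.75, just under 4% of runs, which is below 5%.

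**Arm differences, if that is the meaning.** With 26 per arm, a two-sided t-test has 19% power for a standardized difference of 0.3 and 42% for 0.5.

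**The case against.** The strongest reply is that the screen adds little to an inflation that is already there. Without it, the adjusted results that happen to be significant average 0.36, 0.39 and 0.44, slightly more than after the screen. This is the ordinary effect of selecting on significance in a small sample. The reply stands in this respect: dropping the screen helps only if every coefficient is then reported, significant or not.

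The reply on masking also stands in large part. The heavy losses need mood to act in opposite directions on neural and cognitive change, and nothing in the article gives such correlations. Mood effects in the same direction leave almost no loss.

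A reader might infer more than the article supports:
- That measures are analysed only where the arms differ. The N-back section uses the word that way, but Procedure and the sentence on the regression's purpose speak of changes. A group mean difference cannot be correlated with one person's change in composite score, so individual values are needed in either case. The phrase is ambiguous and does not settle the matter.
- That the two-step rule produces false positives. It does not. Nor does the article call the regression an independent confirmation; it can be read as asking whether a raw correlation survives adjustment.
- That a blank result hides an analysis never done. If change over time is meant, the raw correlation is always computed and can be reported.

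**Conclusion.** The point holds as a minor one. The article fixes a rule under which its named test of prediction is fitted only after a significant unadjusted correlation. Estimates reported under that rule are biased away from zero: substantially for weak associations, and by under 10% for a true 0.40 with 52 participants. An association suppressed by mood can fail to reach the model; the loss runs from about 3% of trials or less to about 58%, depending wholly on assumed mood correlations. These figures also rest on an assumed alpha of 0.05 for the correlation and on both arms being pooled.

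One might go on to say that the trial's conclusions are in doubt. The article does not support that: the neural analysis is labelled exploratory, and no primary or secondary outcome depends on it. The meaning of the neural differences carried forward needs stating. If arm differences are meant, they are a second filter, and one that would often close at this sample size.

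**What to change.** Reword the paragraph as follows:
1. State that the neural measure is each participant's change from baseline to week 2 in every region and task already named (dorsal prefrontal cortex, including the dlPFC, for N-back; dorsal prefrontal cortex and hippocampi for picture encoding), used whether or not the arms differ.
2. Fit the regression adjusted for mood and demographics for each of these measures, whatever the raw correlation shows.
3. Include treatment arm in the model. Without it, a pooled slope can arise merely because ABCR shifts both neural activity and cognition. Add an arm-by-neural-change term as exploratory, since the target is improvement associated with ABCR.
4. Report every coefficient with its 95% confidence interval, and keep raw correlations and whole-brain results as description.

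The cost is a few sentences of plan text, a few more exploratory models and some null results to report. No further data or visits are needed. The interaction term will be imprecise with 26 per arm and should be read from its interval.
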